### Programme delivery

#### Intervention

The New Baby Programme will be delivered by experienced health visitors specifically recruited for the study. They will receive an induction programme designed to familiarise them with the programme and the particular challenges of working with pregnant women whose social circumstances are complex. Training will be delivered by a specialist trainer together with a health visitor experienced in delivering the programme and working with this group of women.

#### Comparator

The Universal Core Programme (UCP) will be delivered by health visitors working in the same area. The UCP is itself a significant service provided to expectant mothers and their children, in the UK. It includes screening tests, immunizations, developmental reviews, information and guidance for parents. There is a strong emphasis on pregnancy and the first year of life [43]. Referral onwards to a range of other services, including specialist services (such as drug and alcohol services) is included in the Healthy Child Programme.

### Recruitment and informed consent

Recruitment will be undertaken via midwives at the three participating hospitals. Eligibility for the study will be determined by midwives who will use a screening tool (in the form of a vulnerability checklist) at the 8–18 weeks booking-in visit. They will briefly inform all eligible women about the study and invite them to take part. They will also provide eligible mothers with accessible, written information and inform them that a specialist nurse may telephone them to provide more details of the study. A senior nurse (a trust manager) from the Ulster Hospital will then telephone mothers to confirm eligibility and establish if the pregnancy is still viable. Women who are not eligible will be thanked for their time. The specialist nurse will ask eligible mothers if they would be interested in taking part and, if so, whether they are willing to be contacted by a named researcher (details of all members of the research team will be included on the information sheet). If the eligible mother is still interested in taking part and is willing for her contact details to be passed to the trial manager, then one of the specialist nurses will contact the research team.

One week following their booking-in visit, a researcher will contact the eligible mother to confirm if she is still willing to take part and, if so, to arrange a suitable time to visit her at her home. During this visit, the expectant mother will be asked to sign a consent form and baseline data will be collected.

During the baseline visit, the researcher will explain the study, including the possibility of any woman receiving the New Baby Programme (NBP) or Management as Usual (MAU), and how this will be determined (i.e. randomisation by a third party not directly involved in the study). In part to recognise their contribution to the study and to encourage retention, participants will be given a £20 gift voucher at completion of each data collection (baseline and 2, 6 and 12 months postpartum) and on completion of the Strange Situation Procedure [55].

### Randomisation

Randomisation is overseen by the School of Nursing and Midwifery (SNM) at Queen’s University, Belfast. It will use a central computer randomisation service (TENALEA) which employs a simple randomisation design in order to maintain complete randomness of the assignment of participants to either the intervention or comparator group.

Having secured written consent from a participant, the researcher will, on return to the office, enter the necessary details into TENALEA. The researcher will be provided with a unique study identifier for the participant but (in order to maintain the blinding of the researcher) not the random allocation. The random allocation will be conveyed by email from TENALEA to a designated officer in the School of Nursing and Midwifery for relaying to the relevant staff in the South Eastern Trust.

### Intervention outcome measures

An overview of the measures and the timetabling of data collection can be found in Table 1. The primary outcome targeted by the New Baby Programme is the parent (primarily the mother)-child relationship, assessed by measuring both maternal sensitivity and child attachment. In the event that the father is the primary carer, we will focus on his relationship with the child. We have chosen to use two measures as together they provide a better assessment of what is a complex, relational outcome. Attachment has been selected because of (i) the links between insecure and disorganised attachment and other parenting dimensions, such as maternal depression [44], substance misuse, neglect and maltreatment [45], and (ii) the centrality of attachment to healthy infant development, as indicated by the association between disorganised attachment and subsequent pathology, such as behaviour problems [46–50] and poor self-regulation [51]. Maternal sensitivity and responsiveness to infants’ needs is recognised as critical to the development of secure attachment [52, 53].

**Table 1 Tab1:** Details and timing of data collection

Outcome	Measures	Average minutes to complete	Baseline, gestation 20 weeks	Infant 2 months	Infant 6 months	Infant 12 months
Attachment	Strange situation	20				X
Maternal sensitivity	CARE-Index	3				X
	Demographics	2	X	X (update)	X (update)	X (update)
Maternal depression	Edinburgh Postnatal Depression Scale (EPDS)	5		X	X	X
Infant questions	Brief questions on feeding and immunisations	.4	X (feeding plans)	X	X (feeding)	X
Lifestyle issues	Brief questions concerning drug use, smoking and alcohol use	1.2	X	X (update)		X (update)
Maternal quality of life	EuroQol (EQ-5D-5L)	5	X	X	X	X
Stress Antenatal stress Parenting stress	STAI-S-6	2	X	X	X	X
	NUPDQ	5	X			
	Parenting stress index, short form (PSI)	10	X	X		X
Parents’ sense of competence	Perceived parenting competence scale (PSOC)	5		X		X
Relationship violence	Brief questions	1	X			X
Social Networks	Medical Outcomes Study (MOS) social support survey short-form 36	5	X			X
Service use		3		X	X	X
Child development	Mullen Scales of Early Learning	15		X	X	X

In addition, a number of secondary outcomes have been selected to assess other aspects of parenting that are known to have a bearing on child development, such as parental mental health, smoking and substance use, neglect and maltreatment.

Measures have been selected primarily for their psychometric properties to support comparison with other studies, particularly Nurse-Family Partnership [54]. The NBP seeks to address similar issues and achieve comparable outcomes, albeit targeted at a different (primarily older) group of pregnant women, making direct comparisons of particular interest. The scheduling of data collection is designed to minimise the burden on participants, and is based on a tried and tested schedule used in a recent study of group Nurse-Family Partnership in England [54].

*Child attachment* will be measured using the Ainsworth Strange Situation Procedure (SSP) [55]. The SSP is a well-validated measure of attachment in infants aged 11–15 months.

*Maternal sensitivity* will be measured using the Infant CARE-Index (ICI). This observational measure uses a 3-min video recording of mother-child play and measures three aspects of maternal behaviour (sensitivity, covert and overt hostility, and responsiveness) and four aspects of infant behaviour (cooperativeness, compulsivity, difficultness, and passivity). These are highly correlated with attachment and also differentiate between abusing, neglecting, abusing and neglecting, marginally more treating and adequate dyads [56]. This means that they will allow us to assess the impact of the NBP on the participant’s parenting profile.

*Maternal depression* will be assessed using the Edinburgh Postnatal Depression Scale (EPDS) when the infant is 2, 6 and 12 months old [57]. This is a well-validated 12-item measure of postnatal depression with high reliability (0.88) and internal consistency (0.87), 86% sensitivity and 78% specificity. The questionnaire will be scored within 24 h of its administration, and any woman scoring above the recommended cut-off (indicating a risk of depression), or who responds affirmatively to the question asking about self-harm, will be brought to the attention of a healthcare professional so that appropriate support can be provided.

*Antenatal stress* will be measured at baseline using The Revised Prenatal Distress Questionnaire (NUPDQ). This is a 17-item measure of pregnancy-specific distress including physical discomforts, financial resources to care for children and pain during delivery [58].

*Postnatal anxiety* will be measured using the Strait Trait Anxiety Inventory Short Form-6 (STAI-6) at baseline and when the infant is 2, 6 and 12 months old [59]. The 6-item short-form of the STAI (STAI-6) has an acceptable reliability (0.82) and produces scores that are similar to those produced with the full-form 20-item STAI across participating groups manifesting normal and raised levels of anxiety. The STAI shows strong criterion, discriminant and predictive validity in perinatal populations [60].

*Parental stress* will be assessed using the Aberdeen Parenting Stress Index, Short Form (ASI-4-SF) at baseline and when the infant is 2 and 12 months old [61]. This is a well-validated 36-item measure of perceived stress in the parenting role. The 36 items are divided into three domains: parental distress, parent-child dysfunctional interaction, and difficult child, which combine to form a Total Stress Score. The ASI-4-SF has a robust test-retest reliability (*r* = 0.84) and internal consistency (*α* = 0.91). High scores on the PSI have been associated with abusive parenting, with some evidence that parenting stress is higher in women with five or more risk factors for child abuse.

Brief questions designed for an earlier study of group Family-Nurse Partnership [54] will be used to explore maternal smoking, alcohol and drug use, and relationship violence.

*Parent’s sense of competence* in the parenting role will be assessed using the Parenting Sense of Competence Scale (PSOC) when the infant is 2 and 12 months old [62]. The PSOC assesses parental competence on two dimensions: Satisfaction and Efficacy, established by factor analysis in a normative nonclinical sample, each with acceptable internal consistency (from 0.62 to 0.72). This is a 16-item Likert-style questionnaire (with a 6-point scale ranging from ‘strongly agree’ to ‘strongly disagree’).

*Maternal health-related quality of life* will be assessed using the EuroQol EQ-5D-5L. This is a standardised measure of health status developed by the EuroQol group that provides a simple, generic measure of health for clinical and economic appraisal [63]. The EQ-5D-5L consists of two pages. The first presents five dimensions of health (mobility, self-care, usual activities, pain/discomfort, anxiety/depression) and asks respondents to indicate their health status by ticking one of the following: no problems, slight problems, moderate problems, severe problems and extreme problems. The second presents a visual analogue scale that goes from 0 (worst health you can imagine) to 100 (best health you can imagine) and asks respondents to indicate with an ‘X’ where on the scale they see themselves. Responses can then be converted to a multi-attribute utility score by applying a UK tariff [64].

*Social support* will be assessed using the Medical Outcomes Study (MOS) Social Support Survey, a 20-item scale measuring four dimensions of support, established using a confirmatory factor analysis: emotional support, tangible support, positive interaction, and affection. Each has an internal consistency of 0.91 or above, and the measure provides a total support score (Cronbach’s alpha 0.97). Stability over time is high for each scale (ranging from 0.72 to 0.78) [65]. Parents’ use of local resources and services will be assessed using questionnaires originally designed for the group Nurse-Family Partnership study, along with brief questions about infant feeding and the take up of immunisation.

*Child development* will be assessed using the Mullen Scales of Early Learning when the child is 2, 6 and 12 months old [66]. The Mullen Scales comprise of five scales (Gross Motor, Visual Reception, Fine Motor, Expressive Language and Receptive Language) which are used for targeting strengths and weaknesses in children. The Mullen test is generally used for evaluating intellectual development and school readiness. Instrument assessments have supported various reliabilities. The median split-half internal consistency was above 0.80 for 3 of the subscales, but 0.79 and 0.75 for Visual Reception and Fine Motor. Test-retest intervals of 1 to 2 weeks and 1 to 24 months scored coefficients of 0.80 and 0.70, respectively.

Overall, response cards will be used for questions that provide a number of response options. All data will be collected during face-to-face interviews in the woman’s home, unless otherwise requested. In the event of respondents having low levels of literacy, the researcher will administer questions orally.

Outcome measures targeted by the intervention will be collected at baseline and 2, 6 and 12 months. Whilst the sample size in this pilot study is not sufficient to inform the power calculations that will be required for a phase 3 study, we will use the available data to estimate the standard deviation and interval estimates (i.e. 95% confidence intervals) of the outcome measures, as this will help inform those calculations (see NIHR guidance on feasibility studies).

### Study outcome measures

#### Primary outcomes—recruitment and retention rates

We will use the screening tools completed by midwives and the records of the senior nurse (see above) to estimate the number of women eligible for the trial and the percentage recruitment rate. Retention of participants will be determined via those for whom data are available at each data collection point. These data will address the feasibility (can we recruit and retain participants) and design (duration, number of recruitment sites required) of any future RCT.

#### Secondary outcomes—acceptability of intervention and study processes

Semi-structured interviews will be conducted with a subsample of mothers at 1 year postpartum, after the completion of other study data collection (thereby retaining the masking of the research team). These semi-structured interviews will explore their experiences of either the NBP or usual services, using a topic guide. Key issues will be the acceptability of the programme, its perceived helpfulness and their experiences of the trial process, including recruitment and follow-up. Women will also be asked about their experiences of randomisation and of data collection. Questions regarding data collection will encompass the frequency of data collection, the time required and the measures themselves. Particular attention will be given to the Strange Situation Procedure, which will be conducted at a specialist facility outside the home.

Women who decline to participate in the trial will also be asked if they are willing to take part in this qualitative study. If they give their consent, we will also conduct semi-structured interviews with them shortly after they decline to ascertain their reasons for not participating.

Because this is a pilot trial, we will conduct semi-structured interviews with key professionals involved in recruitment and referral, to explore their views on the feasibility of our strategy for recruitment, including the timing, materials and required resources. At the end of the study, we will also conduct semi-structured interviews with health visitors delivering a service in both arms of the trial and other key professionals (for example, supervisors, managers, consultants).

#### Researcher blinding

The study has been designed to maximise the chances of the research team (other than the person responsible for data entry) to remain blind to the allocation status of participants, particularly with regard to those conducting data collection. Women have been asked not to disclose their allocation status to those collecting data, and the latter remind women of this prior to each visit. Outcome assessors are also asked to record any indication given of the allocation status of participants during each contact with participants. These will be reported and taken into account as an indication of potential bias.

### Economic evaluation

Economic data, including resource use and unit costs, will be collected in parallel with the trial. Resource use information will be derived at the individual level from parental self-report on use of local resources and health and social services. A resource measurement tool designed and standardised for the group Nurse-Family Partnership study will be used. Health visitors delivering the intervention will record the time spent and activities undertaken in support of the parent-infant dyad.

NBP costs will be calculated using a standard micro-costing (bottom-up) approach and will be based on health visitor salaries plus on-costs (employers’ national insurance and superannuation contributions) and appropriate capital, administration and training costs. Nationally applicable unit costs will be applied to all community health and social care contacts, derived from the Personal Social Services Research Unit (PSSRU), and medications, derived from the British National Formulary. Costs for NHS hospital contacts will be taken from NHS reference costs.

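### Researchers meant to stay blind ask mothers about service use face to face at 2, 6 and 12 months, a foreseeable and avoidable risk of unblinding

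*Protocol article*

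**What the plan says.** Blinding. Under Randomisation, the allocation is withheld from the researcher "in order to maintain the blinding of the researcher". Under Researcher blinding, the research team other than the person doing data entry is to stay blind, "particularly with regard to those conducting data collection". There are two safeguards. The first is addressed to participants: "Women have been asked not to disclose their allocation status to those collecting data", with a reminder before each visit. The second is a log: "Outcome assessors are also asked to record any indication given of the allocation status of participants during each contact with participants". Its entries are to be reported as a sign of possible bias. Ability to maintain blinding is itself a listed secondary outcome of the pilot.

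Service use. Under Economic evaluation: "Resource use information will be derived at the individual level from parental self-report on use of local resources and health and social services". Under Intervention outcome measures, parents' "use of local resources and services will be assessed using questionnaires originally designed for the group Nurse-Family Partnership study". Table 1 marks service use at infant age 2, 6 and 12 months. On mode, the same section says: "All data will be collected during face-to-face interviews", in the home unless the woman asks otherwise, with oral administration where literacy is low. It makes no exception for service use.

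Related provision. Under Secondary outcomes, the semi-structured interviews about NBP or usual services take place only after the other data collection is finished, and the stated reason is to preserve masking.

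**The concern.** Mothers are asked not to reveal their arm. The same research staff then ask them which health and social services they have used, in a trial whose arms differ by a service. An honest answer about how often a health visitor came, or what she did, could point to the arm.

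Two things are at stake. The first is the outcomes that depend on a researcher's handling of the visit: the Mullen scales at 2, 6 and 12 months, and the CARE-Index and Strange Situation at 12 months. Knowledge gained at an early visit could carry into a later one. The second is the blinding outcome. If the study's own form prompts the disclosure, the pilot cannot easily tell a phase 3 team how much unblinding was avoidable and how much comes with the intervention.

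**Working it through.** The document gives no figure to reproduce. The check is a comparison of who asks what, when, and who is to be blind.

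1. **Schedule (Table 1).**

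| | Baseline | 2 mo | 6 mo | 12 mo |
|---|---|---|---|---|
| Service use | – | X | X | X |
| Mullen scales | – | X | X | X |
| CARE-Index | – | – | – | X |
| Strange Situation | – | – | – | X |

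2. **Count of occasions.** Service use is asked at 3 visits. Two of them (2 and 6 months) come before the single CARE-Index and Strange Situation assessments. The third falls at the same time point, with no order stated. At the target of 50 women and full retention, this gives 50 × 3 = 150 administrations, of which 50 × 2 = 100 precede the 12-month visit. These are opportunities for disclosure, not expected disclosures.

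3. **Does the form touch what separates the arms?** The items are not shown, so this is inference. The economic analysis needs a total cost per mother-infant pair in each arm. The only contact log described is kept by the health visitors delivering NBP. For health-visitor contacts in the comparator arm, self-report is the only source the costing text names. The form therefore probably asks about health visiting.

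4. **Would the answer identify the arm?** Not by itself. The Universal Core Programme is also delivered by health visitors. But NBP augments the universal service and is delivered by health visitors recruited for the study with small caseloads, so the frequency or description of contacts could be informative.

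5. **Consistency.** The qualitative interviews about services are postponed to protect masking. The service-use form raises a neighbouring subject three times during follow-up with no separation from the assessor. One hazard is handled in two ways.

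6. **Costing.** NBP is micro-costed from health-visitor inputs, and separately "Nationally applicable unit costs will be applied to all community health and social care contacts". No rule is stated that keeps NBP visits out of the second set.

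**The case against.** The strongest reply is that nothing shows the form discloses anything. It may omit NBP contacts or not distinguish them from other visits, since NBP time has its own record. Both arms see health visitors, and item content and order are details that an article may leave to the full protocol. All of this stands, and it rules out the inference that the questionnaire reveals allocation or that every NBP mother becomes identifiable. What remains is the mode and timing, which the article does fix, and its different treatment of the qualitative interviews.

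Other stronger readings also fail:

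- A reader might infer bias in the pilot's primary outcomes. Those are recruitment and retention, which are not assessor-rated. CARE-Index and Strange Situation are the primary outcome targeted by the intervention.
- A reader might infer biased scoring of those two measures. Both are video-taped, and the document does not say who codes them. Nor does it say that one researcher follows each mother.
- A reader might take the log to cover only volunteered remarks. Its wording covers any indication given, so a revealing service-use answer belongs in it. The log describes no record of what the assessor believes, so an unspoken inference could still be missed.
- A reader might conclude that NBP visits will be counted twice. The text does not say that self-reported NBP visits are valued at unit cost. It only leaves the exclusion unstated.

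It can also be said that a pilot should find out whether its measures unblind assessors. That is fair, but a log alone gives limited help in separating the form's effect from other causes.

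**Conclusion.** The point holds as a foreseeable, repeated and avoidable risk of unblinding: three administrations per retained woman, two of them before the 12-month CARE-Index and Strange Situation. The probability that any one answer reveals the arm cannot be derived from the document, and no percentage should be attached to it.

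The conclusion rests on two assumptions: that the form asks about health visiting in some way, which the costing plan makes likely but does not establish, and that service-use questions are put by the staff who carry out the assessments, as the general statement on data collection implies. If the form omits health-visitor contacts altogether, the risk is much smaller. The reminder and the log are real safeguards. They discourage or record disclosure but do not remove the prompt. The Mullen scales are the most exposed measure, because they are given at the same three visits and no video record is described for them. This is a low-cost improvement and does not threaten the pilot's primary outcomes.

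**What to change.** 1. At each visit, complete the assessor-rated measures before any service-use question.
2. Then collect service use on a sealed self-completed form. Where literacy is low, use a call from the data-entry person, whom the protocol already exempts from blinding. The assessor should not see the answers, and queries on this form should not go back to the assessor.
3. At the start of the 12-month visit, have the assessor record a guess of allocation (NBP, usual care, don't know). Report it by arm beside the existing log.
4. State that the coders of the CARE-Index and Strange Situation videos are blind to allocation and to service-use data.
5. State that NBP visits micro-costed from health-visitor records are excluded from the self-reported contacts valued at unit cost.

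The cost is a reordered visit, one extra item, some calls and two sentences of text. The downside is that some self-completed items may be missing. Replacing self-report with routine records in both arms is not proposed. The protocol mentions NIMATS/CHS only in connection with the characteristics of women approached, declining or recruited, and does not say that these systems hold visit counts.
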